## Abstract

**Background:**

Body dissatisfaction is a growing concern among adolescent females, particularly those living in rural communities where access to supportive mental and physical health resources is limited. High levels of social media use and low engagement in structured physical activity are linked to negative body image, elevated anxiety, and reduced overall well-being in this population. The Hoosier Sport Re-Social intervention was developed to address these challenges by integrating sport participation, social media literacy, and mental skills training in a community-based program designed for adolescent girls.

**Methods:**

This study follows the Standard Protocol Items: Recommendations for Interventional Trials (SPIRIT) guidelines and is structured around three aims. First, we will conduct a cross-sectional study with adolescent girls in grades 6 through 9 to examine the relationship between body satisfaction, physical activity levels, and social media use. Second, we will develop the Hoosier Sport Re-Social intervention using a co-design process that actively involves adolescents, parents, and school staff to ensure relevance and feasibility. Finally, we will conduct a mixed-methods pilot study in two rural middle and high schools to assess feasibility and acceptability. The intervention will be implemented within physical education and health classes over a 6-week period. Primary outcomes will include feasibility indicators such as recruitment, retention, fidelity, and participant engagement. Secondary outcomes will include measures of body satisfaction and social media literacy, while exploratory outcomes will examine changes in psychosocial factors and physical literacy.

**Discussion:**

This study will provide important insights into the acceptability and practicality of delivering a biopsychosocial, school-based intervention targeting body dissatisfaction among rural adolescent girls. Findings will inform future efforts to scale the program and evaluate its effectiveness in improving mental, physical, and cognitive health outcomes.

**Trial registration:**

This trial was prospectively registered with ClinicalTrials.gov (NCT06556719).

**Supplementary Information:**

The online version contains supplementary material available at 10.1186/s40814-025-01695-5.

## Background

Fifty-three percent of American girls are “unhappy with their bodies,” with 46% of 9–11-year-olds actively dieting and reporting body dissatisfaction (generally defined as a negative subjective evaluation of one’s body size, shape, or overall appearance) [1]. This body dissatisfaction is correlated with the development of life-threatening mental health issues (e.g., body dysmorphia, eating disorders, self-harm) [2, 3]. Body dissatisfaction in adolescence is associated with poorer quality of life [4] due to factors such as negative affect [5] and self-talk [6], as well as low self-esteem [7, 8] and self-acceptance [6].

Social media use during adolescence creates potentially serious complications for mental health. The use of social media during adolescence is linked to a significant 189% rise in U.S. hospital admissions for non-fatal self-harm among adolescent females, which has been correlated to increases in body dissatisfaction [9, 10]. Furthermore, there has been a more than 151% [11] increase in suicide rates among adolescent females, and this is associated with the rising trend of increased social media use [12].

Social media significantly impacts adolescent female body image, creating unrealistic appearances through edited images and messages [13–18]. Key issues include exposure to distorted self-images, prolonged exposure to edited content, and unrealistic body portrayals [17, 19, 20]. Importantly, the daily average of screen time for adolescents is 6 to 9 h, and more screen time is correlated with greater body dissatisfaction [21, 22]. Furthermore, age significantly influences the relationship between social media use and body satisfaction, as highlighted in a recent systematic review [23], with younger females being at greater risk of body dissatisfaction due to social media.

Reducing exposure to social media in adolescent females should be a public health priority. Indeed, research underscores the vulnerability of adolescent females, emphasizing the need for targeted interventions and support for body image and social media usage [20], such as supportive school environments teaching media literacy [13, 24]. Currently, research supports multifaceted classroom interventions spanning at least 1 to 4 weeks to address body satisfaction and social media literacy [25]. Despite the promising potential of this work, interventions to improve social media literacy show only a limited effect, and few interventions emphasize targeting populations with increased health disparities (e.g., rural populations) [25, 26]. A recent systematic review on physical activity and healthy digital media usage revealed a significant research gap, with the majority of studies conducted only in high-income areas, with limited work in rural populations [27]. There remains a need for research in low- and middle-income populations, as there is limited available data on the necessity for comprehensive strategies to achieve behavioral change in school-aged children and adolescents [28, 29].

Adolescence, a crucial developmental stage for body image, requires interventions educating at-risk females about social media literacy and promoting positive body image (a holistic appreciation of one’s body, encompassing respect for its functionality, acceptance of its appearance, and the rejection of narrow beauty ideals) [19, 30]. Structured physical activity participation can be a powerful tool to improve body satisfaction in adolescent females [31–33]. In the present study, structured physical activity is defined as any activities that are planned in a formal setting to improve physical fitness or sport-related skill development (e.g., sports, workouts, fitness classes) [34]. Research demonstrates that sports can counteract body dissatisfaction in adolescent females [35]. Similarly, female adolescents who do not participate in sports/physical activity tend to have significantly lower levels of body satisfaction when compared to those who are actively involved in sports [33] or structured physical activity [31–33]. The link between structured physical activity and increased body satisfaction may be influenced by an elevated sense of body appreciation following exercise [31–33]. Additionally, improved physical literacy is associated with increased physical activity and decreased screen behavior [36, 37], which may help reduce social media usage.

Despite the benefits of structured physical activity, alone it may not be sufficient to completely counteract the harmful effects of continuous exposure to negative body image messages prevalent on social media [33]. However, the addition of mental skills training may enhance the intervention’s potential. Mental skills training (e.g., goal setting, positive self-talk) is a helpful, age-appropriate, and easily accessible method for shifting the perspective of adolescent girls toward improved body satisfaction [38]. Engaging in just one session of positive self-talk has been shown to reduce body dissatisfaction and increase the intention to practice body positivity [38, 39]. Additionally, self-affirmations are a proven technique to mitigate the negative effects of body-image concerns induced by social media [40]. Hence, mental skills training can be a valuable addition to a sports-based program targeting body satisfaction in adolescent girls. Figure 1 illustrates this model. The addition of mental skills training may enhance the intervention’s potential effectiveness. Mental skills training (e.g., goal setting, positive self-talk) is a helpful, age-appropriate, and easily accessible method for shifting the perspective of adolescent girls toward improved body satisfaction [38]. Engaging in just one session of positive self-talk has been shown to reduce body dissatisfaction and increase the intention to practice positive body image [38, 39]. Additionally, self-affirmations are a proven technique to mitigate the negative effects of body-image concerns induced by social media [40]. Hence, mental skills training can be a valuable addition to a sports-based program targeting body satisfaction in adolescent girls. Figure 1 illustrates this model.

**Fig. 1 Fig1:**
[figure not shown]
Hoosier Sport Re-Social goal

The primary objective of the proposed study is to develop and evaluate the feasibility of a biopsychosocial intervention designed to improve body satisfaction among adolescent females. This intervention, Hoosier Sport Re-Social,^1^ integrates mental skills training and social media literacy within a sport-based youth development program tailored to the unique needs of adolescent girls in rural schools in the USA. Our central hypothesis is that the intervention, developed through a collaborative co-design process with adolescents, parents, and teachers, will demonstrate both feasibility and acceptability in the rural middle school context. Specifically, we anticipate that the intervention will be practical to implement and well received by the target population, addressing key factors influencing body satisfaction and supporting positive outcomes in physical activity and social media engagement. By focusing on these areas, the study aims to provide a scalable model for improving body satisfaction and promoting healthier behaviors among adolescent females in similar rural settings.

## Methods/design

### Overview

This study is structured into three distinct phases to address body image perceptions and develop interventions for adolescent females enrolled in under-resourced rural middle and high schools (grades 6–9). The first phase, AIM 1, involves conducting a comprehensive needs assessment through community-engaged research to build foundational knowledge about body image, social media usage, and physical activity levels among rural adolescents. This phase aims to identify current physical activity levels and assess facilitators and barriers to positive body image within the adolescents’ context.

In the second phase, AIM 2, the focus shifts to co-designing the Hoosier Sport Re-Social intervention with key community stakeholders. This involves collaborating with adolescents, parents, and teachers to develop a prototype multi-level intervention and implementation protocol. Participant involvement is central to the Hoosier Sport Re-Social protocol. Adolescents, parents, and teachers are not only research participants but also co-creators of the intervention. Through a series of structured co-design sessions, these stakeholders actively contribute to identifying problems, generating solutions, and refining the final prototype, ensuring the program is contextually relevant and responsive to community needs. The goal is to create an intervention that is responsive to the needs and preferences of adolescents, specifically targeting the promotion of a positive body image.

The third phase, AIM 3, involves piloting the Hoosier Sport Re-Social intervention with a sample of 50 adolescents, divided into 25 in the intervention group and 25 in the control group. This phase will evaluate the feasibility and acceptability of the intervention, assessing both trial-related and intervention-specific feasibility indicators. Feasibility refers to the extent to which an intervention can be successfully delivered in a specific setting, considering factors such as recruitment, retention, acceptability, adherence, and implementation fidelity. The overarching hypothesis of the study is that the successful completion of these three phases will result in a feasible and effective intervention protocol for promoting a positive body image among adolescent females in rural settings. Figure 2 provides a timeline of these aims.

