### Aim 3: To establish proof-of-concept and test Hoosier Sport Re-Social's feasibility, acceptability, and appropriateness

#### Aim 3: design

The third phase of the study will evaluate the feasibility of the Hoosier Sport Re-Social intervention (#NCT06556719) with 6th through 9th grade students from a rural middle or high school, conducted twice weekly over an 8-week period (ORBIT Phase Ib). Our assessment will focus on recommended feasibility measures for feasibility studies [28]. Alongside these measures, we will explore outcomes including self-reported weekly moderate-to-vigorous physical activity (MVPA) and physical literacy, body satisfaction, daily social media use duration, various psychosocial factors (such as self-esteem, body appreciation), and psychological needs using the BPNSFS.

Following the initial feasibility test, we will refine and retest the *Hoosier Sport Re-Social* intervention during the subsequent semester. To support intervention delivery, college student mentors—enrolled in upper division undergraduate or graduate public health programs—will collaborate with our research team. These mentors will undergo a 4-week training course before working with the middle or high school students. Their participation in delivering the intervention will be part of their academic coursework, earning them credit hours. The intervention is delivered by trained college students enrolled in upper-division public health and kinesiology courses. This model supports sustainability and scalability by leveraging an existing service-learning partnership between the university and the rural school. It also enhances relatability, as adolescents may feel more comfortable engaging with near-peer facilitators.

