Our hypotheses for Aim 3 include several expectations: achieving full enrollment *(N* = 50), retaining 85% of participants by the intervention’s end, maintaining a 75% attendance rate, obtaining a mean score of ≥ 16 (considered a “good” score) on the Feasibility of Intervention Measure (FIM), AIM, and IAM, and ensuring an 80% fidelity rate in adhering to intervention procedures. Our selection of implementation measures (AIM, FIM, IAM) aligns with core constructs from the Theoretical Framework of Acceptability (TFA) and maps onto RE-AIM dimensions (e.g., implementation and acceptability). This approach supports a structured evaluation of the intervention’s feasibility and future scalability. The Hoosier Sport Re-Social intervention is described in accordance with the Template for Intervention Description and Replication (TIDieR) framework to enhance reproducibility. A structured fidelity checklist has also been developed to monitor delivery, adherence, and adaptations across implementation sessions, ensuring consistency with the intended intervention protocol. Progression to a full-scale randomized controlled trial (RCT) will be considered if the pilot study demonstrates the following: enrollment reaches at least 80% of the target sample (*N* = 50); retention at post-intervention assessment is 85% or higher; session attendance averages 75% or above; fidelity to the intervention protocol is maintained at or above 80% based on fidelity monitoring; and participants report mean scores of at least 16 out of 20 on validated measures of feasibility (FIM), acceptability (AIM), and appropriateness (IAM). These criteria align with recommendations for determining readiness to advance from a pilot to a full-scale trial in behavioral intervention research.

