#### Aim 3: sample size calculation

A target sample size of 50 participants has been selected based on prior recruitment rates from the Hoosier Sport program, which has consistently engaged approximately 60 students per semester and achieved 100% retention over the past two semesters. This sample size will allow us to estimate feasibility indicators such as recruitment, retention, and intervention fidelity with reasonable precision. For example, a sample size of 50 would allow us to estimate a retention rate of 85% with a 95% confidence interval of ± 10%. This level of precision is appropriate for assessing progression criteria to a larger trial. Additionally, although not powered to detect statistical significance, this sample will support estimation of effect sizes related to body satisfaction, social media literacy, and psychosocial outcomes, which will inform future trial design and sample size calculations.

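### The overarching hypothesis claims an effective protocol and the Aim 3 heading claims proof-of-concept, but neither has a body-image success criterion behind it

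*Protocol article*

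**What the plan says.** Two places in the protocol article make a claim that goes beyond feasibility.

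- Methods/design, Overview: "The overarching hypothesis of the study is that the successful completion of these three phases will result in a feasible and effective intervention protocol". The sentence goes on to name positive body image in rural adolescent girls as what the protocol is to be effective for.
- Heading of Aim 3: "To establish proof-of-concept and test Hoosier Sport Re-Social's feasibility, acceptability, and appropriateness". Proof-of-concept is listed separately from the three implementation constructs.

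Elsewhere the article limits itself to feasibility.

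- Background, primary objective: the central hypothesis is that the intervention "will demonstrate both feasibility and acceptability in the rural middle school context".
- Aim 3: design: the specific hypotheses are enrolment of 50, "retaining 85% of participants by the intervention’s end, maintaining a 75% attendance rate", FIM, AIM and IAM means of at least 16, and 80% fidelity. The decision rule is worded "Progression to a full-scale randomized controlled trial (RCT) will be considered if the pilot study demonstrates the following", and its list repeats these measures, with enrolment set at 80% of target.
- Aim 3: sample size calculation: the sample is described as "although not powered to detect statistical significance" and is meant for estimating effect sizes.
- Aim 3: data analysis: the primary objective is feasibility. Body satisfaction (secondary) and body appreciation (exploratory) are analysed by pre-post paired t-tests, then repeated measures ANOVA. No result on either counts as success or failure.
- Abstract, Discussion: evaluating effectiveness is left to future efforts.

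**The concern.** A hypothesis should be open to refutation by the data the study plans to collect. The feasibility part is: each indicator has a threshold. The effectiveness part is not, because no BSQ or BAS-2 result is named that would count for or against it. Proof-of-concept in the Aim 3 heading has the same gap.

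The practical risk lies in reporting. The Overview ties effectiveness to successful completion of the phases, and the only stated marks of success for Aim 3 are process and perception measures. A pilot that recruits, retains and pleases its participants could then be written up as having borne out the overarching hypothesis, even if body image did not change or worsened. The pilot is meant to inform a full trial, so that reading could carry forward.

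**Working it through.** **1. Claim against criteria.** The inputs to the Aim 3 hypotheses and the progression rule are enrolment, retention, attendance, fidelity, FIM, AIM and IAM. None is a measure of body satisfaction, body appreciation or social media use. The output of the rule is consideration of an RCT.

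**2. The plan's own figure.** The only Aim 3 calculation is the precision of an 85% retention rate with N = 50:

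1.96 × √(0.85 × 0.15 / 50) = 1.96 × 0.0505 = 0.099.

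This reproduces the stated ±10%. It concerns retention and carries no information about body image.

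**3. Could a between-arm test support effectiveness?** The Overview has participants "divided into 25 in the intervention group and 25 in the control group". The article gives no effect size, SD or alpha for these outcomes in Aim 3. I assume a standardised difference d between 0.3 and 0.8 and two-sided alpha 0.05. The noncentrality is d × √(25/2) = 3.536 d, and the normal approximation to power is Φ(3.536 d − 1.96).

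| d | 3.536 d | Normal approximation | t-test (48 df) |
|---|---|---|---|
| 0.3 | 1.061 | 18.4% | 18.0% |
| 0.5 | 1.768 | 42.4% | 41.0% |
| 0.8 | 2.828 | 80.7% | 79.1% |

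By the t-test, 80% power needs d of about 0.81. If retention is exactly 85%, complete-case analysis leaves about 0.85 × 25 = 21 per arm. Power is then 16% at d = 0.3 and 35% at d = 0.5, and 80% needs d of about 0.89.

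For 80% power, n per arm = 2 × (1.96 + 0.842)² / d². This gives 63 per arm at d = 0.5 and 175 per arm at d = 0.3, so adding a significance criterion at N = 50 would not rescue the word *effective* for small or moderate effects.

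**4. Could the paired t-tests?** A pre-post test does not use the control group, so it responds to any change over time. Suppose scores drift for reasons unrelated to the programme by 0.3 SD of the change score. A paired test on 25 participants is then significant in about 30% of trials, and on all 50 in about 55%. At a drift of 0.5 SD the figures are 67% and 93%. The size of any drift is an assumption; the article gives none.

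**5. What 25 per arm can give.** In SD units, the 95% half-width for a between-arm difference is about 1.96 × √(2/25) = 0.55. That is useful as an estimate with its uncertainty shown, and too wide for a claim of effectiveness at moderate effects.

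**The case against.** The strongest reply is that this is one word and one heading in an article that otherwise describes a feasibility study. The central hypothesis, the specific Aim 3 hypotheses, the primary objective and the power disclaimer all show how the authors would interpret results. The Aim 2 design section uses *intervention protocol* for the document that co-design produces, so the overarching sentence can be read as an aspiration for that product. This stands as a reason to treat the defect as one of stated claims. It does not remove the conflict between the two hypotheses.

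A reader might also infer three stronger things that the article does not support.

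- *That meeting the thresholds formally establishes effectiveness or proof-of-concept.* The Overview sentence is a hypothesis and the Aim 3 text a heading. The only rule leads to considering an RCT, and process measures are proper inputs for that decision.
- *That body image goes untested.* It is tested, by paired t-tests and repeated measures ANOVA, and the ANOVA text mentions interactions and between-group differences. What is missing is a success criterion.
- *That the thresholds are met equally often whether or not the programme works.* No body-image term enters them, but strict equality also needs process measures to be independent of benefit. Participants who benefit may attend more and rate the programme higher. Nor does a single pass probability measure the problem: at least 43 of 50 retained (85% of 50 is 42.5) has probability 52%, 88% or 99.7% at true retention of 85%, 90% or 95%, and retention is only one of several criteria.

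**Conclusion.** The concern holds as a conflict between stated claims and what the design can show. *Effective* in the overarching hypothesis and proof-of-concept in the Aim 3 heading have no body-image criterion behind them, and they disagree with the Background, the Aim 3 sample size section and the Abstract. The progression rule is sound for its own purpose. The exposure is that passing it is later presented as confirming the overarching hypothesis.

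The planned body-image analyses cannot fill the gap: the paired tests leave out the control group, and a between-arm comparison is weak at small and moderate effects. The power figures rest on 25 analysed per arm, an assumed two-sided alpha of 0.05 and assumed standardised effects; dropout lowers them. The textual conflict rests on no assumption.

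**What to change.** 1. In the Overview, replace *feasible and effective* with *feasible, acceptable and appropriate*, in line with the central hypothesis and the Aim 3 measures.
2. In the Aim 3 heading, remove the proof-of-concept clause, or say explicitly which reported body-image estimate, with its confidence interval, it refers to.
3. In Aim 3: data analysis, report BSQ and BAS-2 as between-arm differences in change from baseline with 95% CIs, and state that no efficacy conclusion will be drawn from this pilot.

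The first two changes are wording, and the stated claim becomes less favourable. The third is a small change to how secondary and exploratory outcomes are reported, because that section now leads with pre-post paired tests. Recruitment, measurement, delivery and the progression criteria stay as they are.
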